### Data acquisition

Demographics collected by written questionnaire and information on adherence and personal circumstances collected during telephone contacts are manually entered into a database. Information on daily physical activity during the week of wearing and daily life data are collected by the worn sensor. These data are collected during the week before the home visits at T_0_, T_1_ and T_2._ Functional tests are performed during the home visits and by self-assessment; data from the functional tests are collected by using the sensor as well as by registration of duration using a stopwatch. For self-assessment, subjects note the date and time at which they perform the weekly self-assessment and shake the sensor five times before and after to mark the self-assessment in the daily life data. All sensor data are transmitted to a tablet by Bluetooth every night and then stored in a web-based interface. Stopwatch times are entered manually into the database.

### Data analysis

Descriptive statistics will be used to describe the baseline and demographic characteristics as well as data on adherence. Changes in daily physical activity and performance on the functional performance tests at T_0_, T_1_ and T_2_ will be analysed by means of Repeated measures ANOVA. Subgroup analyses will be conducted taking into account the potential influence of age, gender, marital status, GFI and BMI. All data will be analysed with Matlab (version 2013a) and SPSS (version 20.0). A p-value lower than 0.05 will be considered statistically significant.

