#### Secondary outcome measures

*Objective daily physical activity based on sensor data*: Baseline (T_0_) information on time spent “active” (standing and walking) will be collected while wearing the sensor for a week before starting the exercise program. A week of wearing will also be used as intermediate and follow-up information on daily activity at T_1_ and T_2_.

*Self-reported daily physical activity*: In addition to objective daily physical activity, self-reported daily physical activity will be measured by questionnaire at T_0_, T_1_ and T_2_. The Short Questionnaire to Assess Health-enhancing physical activity (SQUASH) gives an insight into habitual physical activity
[22]. The SQUASH consists of four domains: A) commuting activities, B) leisure-time activities, C) household activities, and D) activities at work and school. The questions within the four domains are prestructured into frequency, duration and intensity of an activity. Reproducibility and relative validity of the SQUASH for assessing physical activity have been evaluated
[22,23].

*Functional performance*: Functional performance is assessed by means of several clinical tests for physical functioning at T_0_, T_1_ and T_2_. First, subjects are requested to stand up from a chair at a self-selected pace (Sit-To-Stand; STS). STS is commonly used as a test to assess lower-limb strength and balance
[24,25]. Slower test scores are associated with higher fall risk in older adults
[26]. Subjects are instructed to sit still for several seconds, stand up from the chair at their preferred pace and then stand still for several seconds. The STS movement has good inter-rater and test-retest reliability in healthy older adults
[27]. The test is repeated three times if possible.

Second, the Timed Up-and-Go test (TUG) will be used to measure balance and functional mobility. The TUG is a widely used clinical test and is known to be associated with fall risk in older adults
[28,29]. The test protocol includes standing up from a chair, walking 3 m at a preferred speed, turning 180°, walking back and sitting down again. Intra-rater reliability ICC as well as inter-rater reliability ICC of the TUG are excellent
[30]. The test is deemed to be a valid measure of dynamic balance and functional control in older adults
[31]. This test will be repeated two times if possible.

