#### Sample size calculation

Sample size calculation is based on the secondary outcome measure of objective physical activity behaviour as measured with the sensor. Based on earlier studies on the effectiveness of physical activity programs for older adults, it should be possible to reach a 15% increase in objective daily activity within six months
[36]. To detect this difference with 80% power (significance level 0.05), a group of 40 participants completing the entire program is required. Assuming a dropout rate of 20%, a total of 50 participants should be enough to demonstrate an increase in daily activity.

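### Repeated measures ANOVA, as usually run, drops anyone missing one visit and does not isolate the six-month increase the study is sized on; a mixed model with a named T2 minus T0 contrast would serve better

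*Protocol article*

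**What the plan says.** The Data analysis section states that changes in daily physical activity and in the functional tests over T0, T1 and T2 "will be analysed by means of Repeated measures ANOVA", using Matlab 2013a and SPSS 20.0. It sets the criterion as follows: "A p-value lower than 0.05 will be considered statistically significant". It prints no analysis set and no contrast between particular visits.

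The Sample size calculation section rests on sensor-measured activity, a secondary outcome. The target is that "it should be possible to reach a 15% increase in objective daily activity within six months". It then says: "To detect this difference with 80% power (significance level 0.05), a group of 40 participants completing the entire program is required". The inflation is "Assuming a dropout rate of 20%, a total of 50 participants should be enough to demonstrate an increase in daily activity".

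Under Secondary outcome measures, baseline activity comes from one week of wear before the program starts, and "A week of wearing will also be used as intermediate and follow-up information on daily activity" at T1 and T2. The Intervention section gives three months with weekly coach calls, then three months without coach contact.

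**The concern.** Two features of the named method fit poorly with the rest of the plan.

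- **Who is analysed.** Classical repeated measures ANOVA needs a value at all three times. A participant who leaves after T1, or who finishes but has one unusable sensor week, contributes nothing. The 20% allowance is labelled dropout and does not visibly cover failed sensor weeks among completers.
- **What is tested.** The study is sized on an increase within six months. The three-visit omnibus test asks only whether the means differ somewhere. Coach contact stops at three months, so a gain at T1 that fades by T2 is a realistic pattern, and the omnibus p-value cannot tell it from a lasting gain.

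The study has no control arm, so the within-group change is the main evidence on effectiveness, and the Abstract makes that evidence part of the decision to proceed to a randomised trial. The Abstract also expects benefit in participants who are sufficiently adherent. If those lost are the less adherent, a completer-only change could look better than the change in everyone enrolled.

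**Working it through.** **Inputs from the document:** 40 completers, 80% power, significance level 0.05, 15% increase, 20% dropout, 50 enrolled, three visits with one sensor week each.

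**Assumptions (not in the document):** the test is two-sided; the 80% refers to a paired T2 versus T0 comparison; compound symmetry holds for the omnibus test; sensor-week failures are independent, at rates chosen for illustration.

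**1. The plan's own figure.** 40 / (1 − 0.20) = 50. This reproduces exactly. Removing all 10 expected dropouts leaves the 40 on which the 80% is defined.

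**2. Implied effect size.** No SD is printed, so the 40 cannot be derived independently. Solving the noncentral t power equation for n = 40 and 80% gives a standardised change dz = 0.454. A 15% increase then implies an SD of change of 15 / 0.454 ≈ 33% of the baseline mean.

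**3. Omnibus test against the six-month question.** Under compound symmetry the noncentrality is λ = n × 2 × S × dz², where S is the sum of squared deviations of the three visit means from their average, in units of the target gain. The test is F(2, 78), with n = 40 and dz² = 0.2063.

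| Visit means (T0, T1, T2) | S | λ | Power |
|---|---|---|---|
| 0, 1, 1 (early gain, held) | 0.667 | 11.01 | 84% |
| 0, 1, 0 (gain at T1, lost by T2) | 0.667 | 11.01 | 84% |
| 0, 0.75, 1 | 0.542 | 8.94 | 75% |
| 0, 0.5, 1 (linear rise) | 0.500 | 8.25 | 71% |

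The first two rows have identical power, although the six-month gain is the full target in one and zero in the other. The last three shapes that end at the target (rows 1, 3 and 4) show that omnibus power for the same six-month gain also depends on where T1 lies.

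**4. Failed sensor weeks among 40 completers.** If a share f of weeks fails at each visit, the number with all three is 40 × (1 − f)³. Power is for T2 minus T0 at dz = 0.454, with n rounded.

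| Assumed f | With all three weeks | Power |
|---|---|---|
| 0% | 40 | 80% |
| 2% | 37.6 (38) | 78% |
| 5% | 34.3 (34) | 73% |
| 10% | 29.2 (29) | 66% |

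Requiring only T0 and T2 leaves 40 × (1 − f)²: 36.1 at 5% (about 75% power) and 32.4 at 10% (about 70%). Part of the loss therefore comes solely from demanding T1 as well.

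**5. Selection, as an illustration only.** If completers gained 15% and the 20% who drop out did not change, the average over all enrolled would be 0.8 × 15% + 0.2 × 0% = 12%.

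**The case against.** A reader might infer that the stated 80% power is not delivered. The document does not support that. The power is defined on those who complete the program, and the enrolment of 50 already pays for the dropouts. A shortfall needs further loss from failed sensor weeks, and no rate is given. The 70% adherence threshold does not supply one: it judges wear and data collection over the program, and a person wearing the sensor on 5 of 7 days may still yield a usable weekly average.

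A reader might also take the 71% for a linear rise as the true power. It rests on the paired-test assumption and on T1 lying exactly halfway, the least favourable position when T2 minus T0 is fixed. If the study was sized for the ANOVA itself, power at 40 completers is 80% by construction.

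Nor is upward bias demonstrated. It depends on why data are missing, and the document gives no figure for its size.

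Three further points stand. The text does not itself say that only participants with all three visits are analysed; that follows from how the method is usually run. A failed sensor week need not remove anyone from the questionnaire analysis or the stopwatch-timed tests. Missing-data rules and follow-up contrasts are often left to a fuller document, so their absence alone is no finding.

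What remains is the choice that the article does fix: a method that is complete-case in its usual form, with an omnibus test that differs from the quantity used for sizing.

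**Conclusion.** The concern holds as an improvement to a secondary analysis. The primary question is adherence, which is described rather than tested, so this is not a must-fix.

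The mismatch between test and target needs no assumption about missing data. With 40 complete cases, dz = 0.454 and compound symmetry, a vanished and a held gain are equally likely to be significant, at about 84% each.

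The missing-data part is conditional. The stated power stands at 40 completers with usable data, with no reserve beyond that; it would be about 73% or 66% if 5% or 10% of sensor weeks failed. Overstatement of benefit in a completer-only estimate is a plausible risk of unknown size.

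**What to change.** Replace the repeated measures ANOVA with a linear mixed model: visit as a categorical factor, unstructured covariance, REML, using every available visit from all enrolled participants. Name T2 minus T0 in sensor active time, with a 95% CI, as the contrast that tests the 15% target, and treat T1 minus T0 as supportive.

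Add a sensitivity analysis that assumes zero change in dropouts. It is needed because the mixed model keeps partial data but does not remove bias if loss depends on activity that was not observed.

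Keep the one-week measurement windows as they are, so that T0, T1 and T2 stay comparable.

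The cost is a change of analysis wording and slightly more analysis work. SPSS 20 has a mixed-model procedure, and no extra participants or data are required.

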**Discussion:**

The physical activity program driven by mobility monitoring through a necklace-worn sensor and remote feedback using a tablet PC is an innovative method for physical activity stimulation in frail older adults. We hypothesize that, if participants are sufficiently adherent, the program will result in higher daily physical activity and higher strength and balance assessed by physical tests compared to baseline. If adherence to and effectiveness of the program is considered sufficient, the next step would be to evaluate the effectiveness with a randomised controlled trial. The knowledge gained in this study can be used to develop and fine-tune the application of innovative technology in home-based exercise programs.

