### Participants

Fifty subjects will be included. Inclusion criteria will be:

– Age 70–85 years.

– Transitional frailty as measured by the Groningen Frailty Indicator (GFI). The GFI is a screening instrument for level of frailty. Scores range from zero (not frail) to 15 (very frail). Older adults will be considered transitionally frail if they have a GFI score of 4 or 5. This GFI score indicates persons with only a minor elevated chance of loss of functionality and heightened disability
[13].

– Community dwelling or assisted living conditions.

– Ability to walk 10 m without support or using a cane or walker.

– Availability of a telephone.

– Ability to understand instructions regarding the use of the technology and execution of the exercise program.

Persons will be excluded based on conditions that hamper safe execution of the exercise program:

– Total hip or knee replacement in the past 6 months.

– Visual problems to a degree that makes it impossible for the subject to accurately read the questionnaires or walk around safely in his own home.

– Stroke within the last 6 months.

– Parkinson’s disease stage 4 or 5.

– Other neurological conditions that can impair daily functioning (e.g. dementia).

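### One unadjusted 0.05 threshold covers five effectiveness outcomes and the subgroup analyses, without making the six-month sensor outcome that set the sample size the lead test; GFI as a subgroup factor has only two adjacent values

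*Protocol article*

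**What the plan says.** The outcome sections of the protocol article list five secondary outcomes measured at T0, T1 and T2: sensor-measured active time, self-reported activity (SQUASH), and three functional tests (STS, TUG, FTSS). The primary outcome, adherence, is described and compared with a 70% cut-off, without a p-value.

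Under Data analysis, changes in activity and functional performance over the three visits go into repeated measures ANOVA. Then: "Subgroup analyses will be conducted taking into account the potential influence of age, gender, marital status, GFI and BMI". One rule closes the section: "A p-value lower than 0.05 will be considered statistically significant". The section names no lead outcome and no contrast among the three visits, and it does not label the subgroup analyses exploratory.

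The sample size section is more specific: "Sample size calculation is based on the secondary outcome measure of objective physical activity behaviour as measured with the sensor", on the expectation that "it should be possible to reach a 15% increase in objective daily activity within six months".

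On eligibility, the Participants section says: "Older adults will be considered transitionally frail if they have a GFI score of 4 or 5". The scale runs from 0 to 15.

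The abstract's discussion ties these results to a decision: "If adherence to and effectiveness of the program is considered sufficient, the next step would be to evaluate the effectiveness" in a randomised trial.

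**The concern.** The decision to move to a randomised trial has two parts. Adherence has a numerical criterion. Effectiveness has none: there are five outcomes, each analysed by a test over three visits at the same threshold, and nothing in the analysis section says which result answers the question. A reader of the final report could not tell whether an isolated significant result, on SQUASH or TUG for example, counts as effectiveness.

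The form of the test adds to this. The time effect in a three-visit repeated measures ANOVA asks whether the means differ anywhere among T0, T1 and T2. The study was sized on a gain within six months, and coach contact stops after three months. A gain that appears at T1 and is lost by T2 is therefore a realistic pattern, and it would give a significant time effect.

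Finally, the subgroup analyses fall under the same 0.05 rule, and one of the five factors can take only two adjacent values in the population admitted. Subgroup results read as significant could misdirect the choice of population for the next trial.

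**Working it through.** **Inputs.** From the documents: threshold 0.05 for all analyses; five outcomes; three visits; five subgroup factors; 40 completers; 80% power; 15% increase; 20% dropout; GFI 4 or 5. Not given: standard deviation, sidedness and test behind the 40, correlation among outcomes, subgroup sizes. These are assumed below, with ranges.

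**1. The plan's own figure.** The dropout step reproduces: 40 / (1 − 0.20) = 50. The 40 itself cannot be reproduced without a standard deviation. Solving backwards with a paired t-test, 80% power at n = 40 needs a standardised change of 0.454 if two-sided (SD of change 15 / 0.454 = about 33% of baseline) or 0.400 if one-sided (15 / 0.400 = about 37.5%).

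**2. Five outcomes, no true change.** P(at least one p < 0.05) = 1 − 0.95^5 = 1 − 0.774 = 22.6% if the tests are independent. A null simulation (4,000 runs per setting, 40 people, three visits, equally correlated outcomes) gave:

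| Correlation among outcomes | At least one of five significant |
|---|---|
| 0.3 | about 21% |
| 0.5 | 18–19% |
| 0.7 | about 16% |

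**3. Adding subgroups, only if every factor is crossed with every outcome.**
- 25 tests: 1 − 0.95^25 = 72.3%.
- 25 subgroup tests plus the five time tests: 1 − 0.95^30 = 78.5%.
- With correlated outcomes, the simulation gave for all 30 tests about 70% at correlation 0.5, 63% at 0.7 and 47–48% at 0.9.
- Under independence at least 14 tests are needed to pass 50% (13 tests: 48.7%; 14 tests: 51.2%).

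**4. What the three-visit test responds to.** Take standardised means of 0, d, 0 at T0, T1, T2, that is, a gain at T1 that is fully lost by T2. Assume compound symmetry and scale the SD of change to 1, so that the within-person error variance is 0.5. The noncentrality is n × Σ(mean − grand mean)² / 0.5 = 40 × (2/3)d² / 0.5.
- d = 0.454: noncentrality 11.0; with 2 and 78 degrees of freedom, P(p < 0.05) = about 84%.
- d = 0.400: noncentrality 8.5; P(p < 0.05) = about 73%.

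A gain reached at T1 and fully kept (0, d, d) has the same sum of squares, hence the same 84% or 73%. The test cannot tell the two patterns apart.

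**5. Information in a subgroup comparison.** Assume an even 20 v 20 split and an SD of change of 33%. The standard error of the difference is 33 × √(2/20) = 10.4 percentage points. A subgroup difference as large as the whole 15% effect is then detected with about 30% power, and 80% power needs about 2.80 × 10.4 = 29 percentage points. An uneven split would be worse.

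**6. GFI.** With only scores 4 and 5 admitted, the factor has two levels, one point apart on a 0–15 scale. No assumption is needed here.

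**The case against.** The strongest reply is that the lead outcome can be recovered from the text. The sample size section singles out sensor activity and six months, and the abstract states a direction and a reference (improvement over baseline). That is correct, and it rules out saying that the plan has no deciding outcome at all. What stands is that the analysis section, where the 0.05 rule is set, does not use that choice.

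Second, nothing says that any single significant outcome would suffice. The abstract's hypothesis joins activity with strength and balance. If both were required, the false-positive chance would be below 23%. This is fair, but the sentence is a hypothesis and not a decision rule, so the 23% describes what the wording leaves open.

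Third, a reader might infer that a chance finding somewhere is more likely than not. That needs roughly the full grid of five outcomes by five factors. The text speaks only of taking into account the potential influence of the factors, which could mean a few covariates or a subset of outcomes. A reader might likewise infer that the sample will be halved and significance compared between halves. The text describes no such procedure, and time-by-factor terms in the planned model fit its wording equally well. Neither inference is supported.

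Fourth, these are secondary outcomes in an uncontrolled cohort, the adherence criterion is untouched, and a randomised trial would follow. A full analysis plan, not shown, could also set the hierarchy. This limits the weight of the point. It does not remove it, because the article itself states the significance rule and the subgroup list, and effectiveness is half of its condition for the next step.

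**Conclusion.** The point holds in a limited form. The analysis section applies one unadjusted threshold to five outcomes and to the subgroup analyses, and it does not carry forward the outcome and horizon on which the study was sized.

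- **Size:** about 23% chance of at least one significant outcome under no effect if independent, or about 16–21% at correlations of 0.3 to 0.7. The figures of 72–79% apply only under independence and a fully crossed grid that the document does not state.
- **Three-visit test:** it would be significant about 84% of the time for a T1-only gain of the size implied by the 40 completers (two-sided assumption), or about 73% under the one-sided assumption. Both rest on compound symmetry and on an effect size solved backwards from the sample size.
- **GFI:** as a subgroup factor it can say almost nothing about level of frailty. This follows directly from the eligibility criterion.

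The adherence conclusion is not affected. This is a cheap improvement to what may be claimed about effectiveness, not a flaw that invalidates the study.

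**What to change.** In the Data analysis section:

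1. Name the T0-to-T2 change in sensor-measured active time as the single lead test of effectiveness at 0.05. This is the outcome and horizon already used for sizing.
2. Report SQUASH, STS, TUG and FTSS, and the T1 results, as supportive, with estimates and 95% confidence intervals.
3. Examine age, gender, marital status and BMI as time-by-factor terms in the planned repeated measures model, with age and BMI kept continuous. Label them exploratory, with no claim of significance.
4. Drop GFI as a subgroup factor. The baseline split between scores 4 and 5 can still be described.

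The cost is wording only: no extra participants, visits or data. The downside is that fewer results can be called significant.

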#### Sample size calculation

Sample size calculation is based on the secondary outcome measure of objective physical activity behaviour as measured with the sensor. Based on earlier studies on the effectiveness of physical activity programs for older adults, it should be possible to reach a 15% increase in objective daily activity within six months
[36]. To detect this difference with 80% power (significance level 0.05), a group of 40 participants completing the entire program is required. Assuming a dropout rate of 20%, a total of 50 participants should be enough to demonstrate an increase in daily activity.

